### Inclusion and Exclusion Criteria

Individuals aged 18-49 years will be recruited to participate. Inclusion in the LAS stratum will require the occurrence of a substantial first-time sprain up to 2-6 weeks prior to obtaining consent, which limits functional activity for at least 1 day. Participants must be able to walk community distances without an assistive device and with a score of ≤4 out of 10 reported on the numeric pain rating scale (NPRS). Inclusion in the CAI stratum requires a history of at least one significant sprain greater than 12 months prior to consent, continued perceived or episodic “giving way” of the ankle, and reported decreased function on the Foot and Ankle Ability Measure (FAAM) activities of daily living (ADL) subscale (score≤90), FAAM Sports subscale (score≤80), and Cumberland Ankle Instability Tool (CAIT; score<24) [21]. Individuals will be excluded if they have previously undergone ankle surgery, had joint realignment owing to fracture, had recent (within the last 3 months) injury to other lower-limb joints, have a diagnosed connective tissue disorder (eg, Marfan syndrome or Ehlers-Danlos syndrome), have a neuromuscular disease or balance impairment (eg, visual or vestibular disorder) that precludes standing or walking, are pregnant, have nonremovable casting, or are unable to walk at enrollment.

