### Statistical Analysis

To assess whether the addition of the rocky treadmill intervention to standard-of-care physical therapy improves rehabilitation, 4 repeated measurements of several outcomes (eg, CAIT and FAAM) will be measured over the active intervention period of the study. The data will be analyzed using an analysis of covariance–type linear mixed-effects model with Group, Time, and Group×Time variables as fixed effects and subject-specific variables {intercepts, slopes} as random effects. The null hypotheses for both LAS and CAI populations are that the slopes of the control groups equal those of the treatment groups.

To identify predictors and mediators of successful or unsuccessful rehabilitation outcomes, a 2-level (hierarchical) Bayesian model will be used to connect participant-specific responses to 6 explanatory variables: {X1, . . . , X6} = {age, sex, body mass index, pain intensity, weight-bearing status, and initial injury severity} to the subject-specific variables {intercepts, slopes}. A directed acyclic graph detailing the results of the Bayesian linear model will be developed (Figure 3). The regression parameters from the hierarchical Bayesian model will be estimated using Bayesian inference with Gibbs Sampling software, which creates a Markov chain Monte Carlo simulation of all regression parameters.

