**Figure 3 figure3:**
[figure not shown]
The direct acyclic graph of the Bayesian model acts like a causal diagram. In the model, the explanatory variables {X1, . . . , X6}: age, sex, BMI, pain intensity, weight-bearing status, and initial injury severity. These variables causally affect the subject-specific slopes and the y-intercepts. However, the slopes and y-intercepts of the responses are not directly observed, so they are considered latent variables. In the diagram, the shaded circles are directly observed variables, and the unshaded circles are latent variables. The Bayesian model has 2 levels of hierarchy: the first one establishes the best fit line that goes through the observed subject responses; the second one establishes how the explanatory variables {X1, . . . , X6} affect the slopes and y-intercepts. The regression parameters {η_0_, . . . , η_6_} are those that affect the slope of the subject responses and, as such, are particularly important because they affect the healing rate. Variables that significantly affect the healing rate will be retained in the model if the credible intervals for the regression parameters {η_0_, . . ., η_6_} do not include 0.

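### The LAS predictor model omits time since injury, so a covariate that tracks recency, chiefly pain, may be retained and read as a cause of healing rate

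*Protocol article*

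**What the plan says.** Inclusion and Exclusion Criteria admits LAS participants on the "occurrence of a substantial first-time sprain up to 2-6 weeks prior to obtaining consent", read here as a window of 2 to 6 weeks. LAS participants must also be "able to walk community distances without an assistive device and with a score of ≤4 out of 10" on the pain scale. CAI participants need a "history of at least one significant sprain greater than 12 months prior to consent", with no upper limit.

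Statistical Analysis describes two models that bear on this point:

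- The treatment model has "Group, Time, and Group×Time variables as fixed effects and subject-specific variables {intercepts, slopes} as random effects".
- The two-level Bayesian predictor model links each participant's intercept and slope to six variables: "age, sex, body mass index, pain intensity, weight-bearing status, and initial injury severity".

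The Figure 3 legend likens the graph to a causal diagram and says of the six: "These variables causally affect the subject-specific slopes and the y-intercepts". A variable stays in the model as affecting the healing rate if the credible interval for its slope coefficient excludes 0. Time since injury is in neither model. The only other adjustment mentioned is for treatment dosage, in the Discussion.

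**The concern.** The outcome of the predictor model is each participant's recovery slope from enrolment. If recovery after an acute sprain is steep early and flatter later, someone who enters at week 2 has a steeper slope ahead than someone who enters at week 6. Pain at entry would also tend to fall over those weeks. Days since sprain is then a common cause of entry pain and of the slope. A causal diagram that leaves it out assigns its effect to whichever listed variable follows it.

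At stake is the secondary aim of finding what predicts and mediates outcome: pain could be reported as driving the healing rate when it only marks how recent the injury is. An article can leave many details to a fuller plan. Here, however, it prints a closed, numbered covariate list together with a causal reading and a retention rule.

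**Working it through.** **1. Sample size used.** Power and Sample Size gives 62 per group and 20% dropout: 62/(1 − 0.20) = 77.5, rounded up to 78. Two arms give 78 × 2 = 156 in LAS, and two strata give 312. The article's figures reproduce, and n = 156 is used below.

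**2. Why recency could matter (assumed).** Suppose the functional deficit decays exponentially with time constant τ. The ratio of a week-2 entrant's slope to a week-6 entrant's is exp(4/τ): exp(4/8) = 1.6 for τ = 8 weeks and exp(4/3) = 3.8 for τ = 3 weeks. Simulating this with entry uniform over weeks 2-6 put the share of slope variance explained by recency at 10-36%. Neither the curve nor τ is in the documents.

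**3. False retention without time since injury.** Let r be the size of the pain-recency correlation and g that of the recency-slope correlation. Let pain have no effect of its own.

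- Induced pain-slope correlation: r·g
- Expected test statistic: z = √n · rg / √(1 − r²g²)
- Chance that the 95% interval excludes 0: Φ(z − 1.96) + Φ(−z − 1.96)

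Here g = √0.10 = 0.316 or g = √0.36 = 0.6. A 95% interval from an ordinary regression with one covariate stands in for the credible interval.

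Example with r = 0.3 and g = 0.316: rg = 0.0949, z = 12.49 × 0.0949/0.9955 = 1.19, and the chance is Φ(−0.77) + Φ(−3.15) = 0.22.

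| r | z, recency explains 10% | False retention | z, recency explains 36% | False retention |
|---|---|---|---|---|
| 0.1 | 0.40 | 7% | 0.75 | 12% |
| 0.2 | 0.79 | 12% | 1.51 | 33% |
| 0.3 | 1.19 | 22% | 2.29 | 63% |
| 0.49 | 1.96 | 50% | 3.84 | 97% |

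Simulation of the same settings gave 6% and 11%, 13% and 31%, 22% and 62%, and 48% and 97%, within two points of the formula.

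**4. With time since injury included.** The partial correlation of pain with the slope is then zero and the rate returns to nominal. Simulation gave 4-6% over r from 0 to 0.7 and g from 0 to 0.5.

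**5. Effect of the entry limit on pain.** Cutting integer pain scores at 4 under the decay model (τ 3-8 weeks) weakened the pain-recency correlation to between −0.19 and −0.43. Pain was still falsely flagged in 12-93% of simulated trials, against 3-7% with time since injury included.

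**6. Treatment comparison.** With time since injury omitted, the simulated mean group effect was about 0 (true value 0) and type I error was 4-7%. Including it only lowered the standard error: from 0.160 to 0.153 at g = 0.3, and to 0.139 at g = 0.5.

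**The case against.** The strongest objection is that every correlation above is assumed. At r = 0.1 the excess over 5% is small, and the limits on pain and walking at LAS entry narrow the two covariates most likely to track recency. This stands: the size cannot be fixed from the documents, and an honest range starts close to nominal. Step 5 shows that narrowing weakens the problem without removing it.

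A second objection is that a marker of recency is still a valid predictor. That is correct for prediction, and it is why softer wording would be a sufficient remedy. It does not rescue the legend, which claims cause.

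Three stronger readings are tempting, and the documents do not support them:

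- A reader might infer that the treatment effect is biased, because time since injury is missing there too. Allocation is randomised, so the Group×Time contrast is unbiased. Random slopes already represent between-person variation in recovery. Under the decay model, the gain in information for that contrast is 0-3% if baseline FAAM is adjusted for, which the covariance-type description of the model suggests but does not spell out. It is 10-54% if baseline FAAM is not adjusted for. Adjustment there is optional.
- A reader might infer that LAS and CAI are pooled in the predictor model with no term for stratum. The article does not say so. The hypotheses, sample size and reinjury analysis are framed by injury type, which makes separate fits the more natural reading.
- A reader might infer that all six covariates are affected. Nothing suggests that age, sex, body mass index or initial injury severity track days since sprain.

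**Conclusion.** The point holds for the LAS predictor model. A baseline variable that is known at entry and is a plausible common cause is missing from a model whose coefficients are read causally and screened by whether the interval excludes 0. Pain intensity, and possibly weight-bearing status, may therefore be credited with the effect of recency.

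The size ranges from barely above nominal to near-certain false retention. It depends on two correlations that the documents do not give, and on approximating the Bayesian model by a regression with one covariate. The consequence is confined to the secondary aim; the primary randomised comparison remains valid. The change is worth making because it is nearly free.

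**What to change.** 1. In the LAS predictor model, add days from sprain to consent as X7, acting on both intercept and slope, and add it to the Figure 3 graph.
2. State that the predictor model is fitted within each stratum. If it is pooled, add an LAS/CAI term that acts on the slope.
3. If time since injury is not added, replace the causal wording in the Figure 3 legend with predictive wording.

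The cost is plan wording and one or two more parameters; the sprain date is already needed for eligibility. The interval for pain changes by the factor √[(1 − g²) / ((1 − r²)(1 − r²g²))]. At r = 0.49 this is √[0.90/(0.760 × 0.976)] = 1.10 when recency explains 10% of slope variance, and √[0.64/(0.760 × 0.914)] = 0.96 when it explains 36%. The interval is thus at most about 10% wider over the range considered.

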### Longitudinal Tracking of Reinjury

Injury count data derived following completion of the intervention will be employed to assess secondary preventive effects of the control and experimental treatments in the LAS and CAI strata. These follow-up data will be collected for 18 months. Both in-network and out-of-network medical care provided to service members will be captured by the MHS. Each recruiting site will conduct a chart review of the electronic medical record at the 6 posttreatment time points to assess for any additional medical care provided for ankle injuries in order to include physical therapy or surgical care. Participants will also be contacted directly to establish any secondary injury outcomes that were self-managed.

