To analyze the effect of the treatment on long-term reinjury rates between the 2 arms of the study, we will fit both logistic regression–type generalized linear mixed-effects (GLME) models to the data as well as Cox regression time-to-event models. The data that will be used in the analysis will be those obtained at baseline and during the postintervention period. In the GLME analysis, the response data will be (1) the self-reported survey instrument measure from the Patient-Reported Outcomes Measurement Information System and (2) the binary reinjury report (1/0). The GLME model will have Group, Time, and Group×Time as fixed effects and will use subject-specific variables {intercepts, slopes} as random effects. The null hypothesis of the GLME model is that the regression parameters associated with the Group and Group×Time effects are zero. In the Cox regression analysis, the response will be the time of suspension or the event along with a binary indicator of reinjury status, and the covariate will be Group. The null hypothesis of the Cox regression analysis is that the regression parameter associated with Group is equal to zero. In all analyses, a Bonferroni-type correction to the hypothesis test’s *P* values or α levels will be used to account for multiple testing.

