### Power and Sample Size

The estimated sample to identify a minimum difference of 1 point in the FAAM between treatment groups across 4 time points in the intervention period was 17 participants per group for an estimated power of 90% and an α value of .05. To measure the effect of the long-term binary reinjury rates with 6 time points in a GLME model, a sample of 62 participants per group provided 80% power, assuming a 10% difference in the proportion between the treatment groups and similar trends between groups. Assuming a 20% rate of dropout throughout long-term follow-up, the required sample size is 78 participants per group. Between the 2 injury types (LAS and CAI), a total of 312 participants will be recruited for this study across the multiple sites.

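### Long-term reinjury is tested by two models of equal standing with no deciding result, and the stated 80% power covers one GLME contrast with no allowance for the planned Bonferroni split

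*Protocol article*

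**What the plan says.** Under Statistical Analysis, the article takes the effect of treatment on long-term reinjury as one question and announces two model families for it: "we will fit both logistic regression–type generalized linear mixed-effects (GLME) models to the data as well as Cox regression time-to-event models". Each has its own null. For the first, "The null hypothesis of the GLME model is that the regression parameters associated with the Group and Group×Time effects are zero". For the second, "The null hypothesis of the Cox regression analysis is that the regression parameter associated with Group is equal to zero". The GLME uses baseline and postintervention data, with subject-specific intercepts and slopes as random effects. The paragraph ends: "In all analyses, a Bonferroni-type correction to the hypothesis test’s *P* values or α levels will be used to account for multiple testing". It does not say which tests form the family or how many there are.

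Three other places bear on the point:

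- Longitudinal Tracking of Reinjury says the injury data serve "to assess secondary preventive effects of the control and experimental treatments in the LAS and CAI strata".
- Power and Sample Size bases the reinjury calculation on a binary outcome at six time points in a GLME. It assumes a difference of 10% between arms and similar time trends in both. The result is 62 per group for 80% power, then 78 per group after 20% dropout. "Between the 2 injury types (LAS and CAI), a total of 312 participants will be recruited".
- Outcome Measures makes the FAAM the primary outcome.

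**The concern.** Two tests of equal rank address one question, and the text gives no rule for the case where one rejects and the other does not. The prevention conclusion would then rest on which result is put forward.

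The Bonferroni sentence limits false positives but does not choose between results that differ. It also has a price: alpha is divided among overlapping tests of the same question, while the sample size was derived for a single contrast.

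Reinjury is not primary, but the stakes are real. The FAAM calculation needs 17 per group and the reinjury calculation 62, so reinjury drives the 312. Lower risk of injury recurrence is also part of the hypothesis in the Abstract and the Discussion.

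**Working it through.** **1. The plan's own figures.** Dropout: 62 / (1 − 0.20) = 77.5, rounded up to 78 per group. Total: 78 × 2 arms × 2 injury types = 312. Both reproduce, and they show that each injury type was sized on its own.

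The 62 cannot be checked, because neither the base rate nor the within-person correlation ρ is given. It is attainable. With six measurements, n = n₁(1 + 5ρ)/6, where n₁ is the size for a single comparison of proportions.

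- 20% vs 10%: n₁ = 199, so ρ ≈ 0.17 gives about 62.
- 30% vs 20%: n₁ = 293, so ρ ≈ 0.05 gives about 62.

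The 62 is therefore taken as given.

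**2. Which tests could share alpha.**

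- Two: the GLME null tested jointly, plus Cox; or one named test in each of two strata.
- Three: Group, Group×Time and Cox in one stratum.
- Six: those three in both strata.

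**3. Power after the split.** Assume the 80% refers to a two-sided test at .05. The standardized effect at 62 per group is then 1.960 + 0.842 = 2.802. With k tests, power = Φ(2.802 − z), where z is the two-sided critical value at .05/k. The size that restores 80% is 62 × [(z + 0.842)/2.802]², before dropout.

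| k | alpha per test | z | power at 62 per group | n per group for 80% |
|---|---|---|---|---|
| 1 | .05 | 1.960 | 80% | 62 |
| 2 | .025 | 2.241 | Φ(0.560) = 71% | 76 |
| 3 | .0167 | 2.394 | Φ(0.408) = 66% | 83 |
| 6 | .0083 | 2.638 | Φ(0.163) = 57% (0.565) | 96 |

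**4. Does the GLME null contain the contrast that was sized?** In a GLME with Group, Time and Group×Time, the log odds ratio between arms at time t is β_G + β_GT·t. The Group coefficient alone is the difference at Time = 0, so it depends on how time is coded, and baseline data are in the model. The sizing assumes similar trends, that is β_GT = 0, and so concerns one difference common to the follow-ups. With the interaction in the model, the matching contrast is the average over the six follow-ups, β_G + β_GT·t̄, where t̄ is their mean time. This is not the Group coefficient unless β_GT or t̄ is zero. A joint test of both parameters is not the sized contrast either, because it spends a degree of freedom on an interaction that the sizing assumes absent.

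**5. How often might the models disagree?** Two simulations with 62 per group and six intervals give an illustration only. Both use a logistic GEE in place of the GLME.

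- Assumed 40% vs 20% reinjured, frailty SD 1: the average Group test and Cox disagreed at .05 in 16% of trials, or 22% if the effect wanes.
- Assumed 8% per interval for a typical participant, random-intercept SD 1, log odds ratio −0.7: the Group coefficient and Cox disagreed in 29% of trials, the joint test and Cox in 19%.

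These inputs are not the protocol's, and the tests in both simulations had well under 80% power.

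**The case against.** The strongest reply is one of scope. This is a condensed article, the outcome is not primary, and ranking two models or listing a Bonferroni family is often left to the statistical analysis plan, which is not shown. The GLME and Cox models also address different quantities, and each could be reported for its own. The sizing paragraph already points to the GLME and, through its similar-trends assumption, to a Group effect.

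Part of this stands. The article need not list every test. But it does more than leave detail out: it fixes both models, both nulls and an alpha correction, and beside them a power figure that matches only one contrast without that correction. That mismatch is in the text itself.

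Three stronger readings are tempting and are not supported:

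- **A pooled analysis competes with the stratum analyses.** The reinjury paragraph has no stratum term, and a reader might infer pooling. No pooled reinjury analysis is announced, and both the tracking section and the 78 × 2 × 2 sizing point to analysis by stratum.
- **The false-positive rate is inflated.** It would be if every test were run at .05, but the correction is stated. In the second simulation, with no true effect and Bonferroni over three tests, at least one rejected in 3.8% of runs.
- **The GLME counts as positive if either parameter reaches .05.** The null reads more naturally as a joint one. Disagreement rates built on the either-or reading should not be used.

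**Conclusion.** The point holds as a matter of decision rule and power, not of type I error. One secondary but sample-size-setting question has two tests of equal standing. No result is named as deciding, and the stated 80% belongs to a single GLME contrast that neither stated null isolates. Testing under the stated correction gives about 71%, 66% or 57% power for two, three or six tests.

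These figures assume that the 62 per group is right, that its 80% refers to a two-sided .05 test, and that alpha is split equally over reinjury tests only. If the family also takes in other outcomes, power is lower. Disagreement between the GLME and Cox tests of roughly 16–29% is plausible but rests on assumed event rates, and the conclusion does not depend on it. The point should be corrected, but it does not touch the FAAM analysis.

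**What to change.** In Statistical Analysis:

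- Name one deciding reinjury test: the Group effect averaged over the six follow-ups in the GLME, estimated separately in LAS and CAI.
- Label the Cox model and Group×Time as supportive, with no alpha.
- State the alpha for each stratum, and hence what the Bonferroni-type correction covers for reinjury.

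In Power and Sample Size, restate the power to match. It is 80% if each stratum is tested at .05, or about 71% at the first Holm step if alpha is shared over the two strata. Holding 80% at .025 would take 76 per group before dropout and 76/0.80 = 95 after it, or 95 × 4 = 380 in all. Restating the power at 312 is the alternative that needs no more participants.

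The change is wording only. Its cost is that a Cox or Group×Time result could not support a reinjury claim if the named test fails. If the unseen analysis plan already fixes this, the article's paragraph only needs to be aligned with it.

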**Methods:**

A multisite, parallel randomized clinical trial will be performed among service members aged 18-49 years being treated for LAS and CAI in military treatment facilities in the United States. Participants randomly assigned and allocated to receive the experimental intervention will be provided up to 12 sessions of training on an uneven terrain treadmill over a 6-week treatment course to supplement standard rehabilitation care. Treatment intensity of the rehabilitation exercises and treadmill training will be progressed on the basis of patient-perceived intensity and treatment responses. Outcome measures will include patient-reported outcomes, functional assessments, performance measures, and biomechanical measures. Investigators collecting outcome measures will be blinded to treatment allocation. Reinjury rates and patient-reported outcomes of function will be tracked over 18 months following treatment.

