### Intervention

#### Overview

Once consented and enrolled, participants will be randomly assigned to either the experimental or control arm at each site using a concealed, random blocked sequence. Stratified randomization will be used to ensure an equal number of men and women are assigned to both the control and experimental groups in the LAS and CAI strata. Group allocation information will be concealed using a password-protected electronic form that will be opened by an uninvolved research staff member and communicated to the treating clinician. Both experimental and control groups will be provided standard rehabilitation care—treatment that is guided by the recent revision of the clinical practice guideline promulgated by the Academy of Orthopaedic Physical Therapy [16] on the basis of clinician experience and patient values.

Participants allocated to the experimental group will also be provided a complementary progressive treatment under the supervision of a licensed physical therapist, consisting of walking on a custom uneven-terrain treadmill (Woodway, Inc) (Figure 1) that simulates negotiation of rocky terrain (Multimedia Appendix 1) [22] for approximately 30 minutes, twice weekly, for a maximum of 12 treatments until discharge from rehabilitation. Treatment will be advanced through 3 phases of activities based on observed performance and the participant’s perceived difficulty and symptom response. Each phase will contain activities that are broadly grouped by the intensity of the proprioceptive stimulus and will be completed on the uneven treadmill. All treating physical therapists will adhere to a single training protocol to ensure standardized delivery of the uneven treadmill training across all the participating sites.

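### The reinjury comparison leaves out the weeks between randomisation and discharge, so it is not a from-randomisation comparison and can be biased in either direction

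*Protocol article*

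**What the plan says.** All references are to the Protocol article.

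- **Randomisation comes first.** Intervention, Overview: "Once consented and enrolled, participants will be randomly assigned to either the experimental or control arm at each site". Treatment follows.
- **Treatment takes weeks.** The abstract describes "up to 12 sessions of training on an uneven terrain treadmill over a 6-week treatment course" for the experimental arm. The Overview ends this training at discharge from rehabilitation, with a cap of 12 treatments, so its length varies by participant.
- **Reinjuries are counted afterwards.** The section Longitudinal Tracking of Reinjury states: "Injury count data derived following completion of the intervention will be employed to assess secondary preventive effects of the control and experimental treatments". It adds: "These follow-up data will be collected for 18 months". The sources are direct contact with participants and a "chart review of the electronic medical record at the 6 posttreatment time points".
- **The analysis uses the same window.** Statistical Analysis, introducing both the generalized linear mixed-effects (GLME) model and the Cox model: "The data that will be used in the analysis will be those obtained at baseline and during the postintervention period". The GLME null is that the "regression parameters associated with the Group and Group×Time effects are zero". The Cox model has Group as its covariate, and its time origin is not stated.

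**The concern.** Read together, these sections place any ankle reinjury between randomisation and discharge outside the comparison meant to show secondary prevention. Those weeks are not neutral:

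- Participants in the lateral ankle sprain stratum enter 2 to 6 weeks after injury, and the Introduction calls recurrence common in the first 12 months.
- Only the experimental arm is exposed to the uneven treadmill. The treatment phases include brace weaning, obscured vision, load carriage and optional running on that surface.
- If the added training provokes reinjuries, or prevents them early, neither effect reaches the reinjury analysis.

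There is also a problem of origin. Randomisation makes the arms comparable when it is done, not at discharge. If time to discharge differs by arm, the 18 months start at different distances from the injury and from randomisation.

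Reinjury is not the primary outcome, which is the FAAM, but it determines the trial's size, so its comparison should keep the protection of randomisation.

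**Working it through.** **The plan's own figures.** Power and Sample Size gives 62 per group for reinjury, 20% dropout, and 78 per group. Check: 62 / (1 − 0.20) = 77.5, rounded up to 78; 78 × 2 arms × 2 strata = 312. Both reproduce. The 62 itself cannot be verified, because the base rate and within-subject correlation are not given. This point does not depend on it.

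**How much time is left out.** The treatment window is up to 6 weeks. Follow-up is 18 months = 18 × 52.18 / 12 = 78.3 weeks. Let m be the hazard during treatment relative to afterwards (assumed). The share of all reinjuries that falls in the omitted window is then 6m / (6m + 78.3):

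| m | Share omitted |
|---|---|
| 1 | 6 / 84.3 = 7% |
| 2 | 12 / 90.3 = 13% |
| 3 | 18 / 96.3 = 19% |
| 5 | 30 / 108.3 = 28% |

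**What omission can do to the difference.** Let r be the risk of reinjury during treatment and p the risk afterwards, with subscripts c (control) and e (experimental). The risk from randomisation is 1 − (1 − r)(1 − p), and the difference is

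D = [1 − (1 − r_c)(1 − p_c)] − [1 − (1 − r_e)(1 − p_e)].

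The plan gives a 10-point difference but no base rate. I assume p_c = 20% and p_e = 10%, read as cumulative post-treatment risks. All r values are assumed. The post-treatment analysis shows 10 points in every row.

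| r_c | r_e | Control from randomisation | Experimental from randomisation | D |
|---|---|---|---|---|
| 3% | 3% | 1 − 0.97 × 0.80 = 22.4% | 1 − 0.97 × 0.90 = 12.7% | 9.7 points |
| 3% | 6% | 22.4% | 1 − 0.94 × 0.90 = 15.4% | 7.0 points |
| 5% | 10% | 1 − 0.95 × 0.80 = 24.0% | 1 − 0.90 × 0.90 = 19.0% | 5.0 points |
| 5% | 2% | 24.0% | 1 − 0.98 × 0.90 = 11.8% | 12.2 points |

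With equal treatment-phase risk the omission hardly matters (9.7 against 10). With unequal risk the post-treatment figure overstates the benefit in rows 2 and 3 and understates it in row 4. The calculation covers omitted events only. It does not model differences between arms in the timing of discharge.

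**The case against.** **Post-treatment reinjury is the declared target.** The article consistently frames secondary prevention as what happens after treatment, and the omitted window is only about 7% of the time from randomisation. This stands as a reason to keep the post-discharge analysis. It does not make that analysis a randomised comparison from its own starting point, nor does it justify having no comparison that includes the treatment weeks.

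**The documents do not show a direction.** A reader might infer that the omission favours the experimental arm because of its added exposure. That needs treatment-phase rates by arm, which are not given; early protection would push the other way. Nor does the article say who decides discharge, so a claim that unblinded clinicians set the start of follow-up is not supported. On-treatment injuries may well be recorded as adverse events under the full protocol, which is not shown. The point is only that they are outside the stated reinjury comparison.

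**The mention of baseline data.** A reader might also infer that the binary GLME contains a baseline row in which reinjury is impossible, so that its Group coefficient tests a baseline contrast. The text does not establish this:

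- The data-window sentence covers two GLME responses, one of them a survey measure for which a baseline value is natural.
- The power statement plans the binary model with 6 time points, matching the 6 posttreatment ones; a baseline row would make seven.
- The null covers Group and Group×Time, and the coding of Time is not stated.

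Even if such a row were present, the joint test of both parameters would barely change. A simulation assumed 62 per arm, six visits, 20% versus 10% per visit, random-intercept SD 1 and a marginal logistic model in place of the GLME (300 runs). It gave 77% power without the row and 79% with it. With no true effect, rejection was 5.7% without and 3.0% with it.

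**Conclusion.** The concern holds in this form: as written, the reinjury analyses exclude events between randomisation and discharge, an interval of up to about 6 weeks in which the arms differ in exposure by design. The comparison can therefore depart from the from-randomisation effect in either direction. Under the assumed rates above, a 10-point post-treatment difference corresponds to anything from 5.0 to 12.2 points from randomisation, and to 9.7 if treatment-phase risk is equal. These figures rest on assumed risks and show what is possible; they do not estimate what will happen in this trial. The exclusion itself rests on the article's explicit wording in two sections. It should be corrected, and correcting it is cheap.

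**What to change.** In Longitudinal Tracking of Reinjury and in Statistical Analysis:

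1. State that the reinjury clock starts at randomisation in both arms, for the Cox and the GLME analyses.
2. Count every ankle reinjury from that point, including those during treatment. The first posttreatment chart review and participant contact can reach back to randomisation, which keeps the 6 planned time points.
3. Report treatment-phase reinjuries separately by arm.
4. Keep the post-discharge analysis as a named secondary analysis, with its origin stated.

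The cost is mainly wording. Existing record review and contact must cover about 6 more weeks per participant. The real concession is that the post-treatment question becomes secondary to the from-randomisation one.
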